### Statistical methods

The effect of the intervention on the primary and secondary outcomes will be assessed by comparing median/percentage outcomes between control and intervention cluster periods and also in the time trends of intervention cluster periods using a non-parametric Kruskal-Wallis test and Pearson’s chi-square statistic, respectively.

Generalized linear mixed modeling at the individual patient level will be used for analyzing the effect of the performance feedback intervention on the primary outcome (door-to-groin time). This will allow us to appropriately account for the different observation cluster periods (both control and intervention) and the hierarchical structure of the data [40]. The model will contain fixed effects for intervention (yes/no), calendar time (month) to account for autonomous time trends, patient characteristics (i.e., patients’ age, sex, NIHSS score at arrival, location of the proximal intracranial occlusion, and onset-to-door time) [40], and a random effect for the hospital. This model enables us to estimate the variance of the outcome of interest (door-to-groin time) at the hospital level (inter-cluster variation) and individual level (intra-cluster variation), which in turn enables us to estimate the total effect of the performance feedback intervention. The increase in the variance due to the clustering will be quantified by the variance inflation factor. In sensitivity analyses, we will estimate the impact of the duration of exposure to the performance feedback intervention, the effect of moving from control to the intervention condition, and/or interaction of both factors on the primary outcome [41].

Multivariable normal models will be used for imputation of missing values, using available data on patient characteristics, structure, and care processes.

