**Methods:**

PERFEQTOS is a stepped wedge cluster randomized trial in 13 hospitals in the Netherlands providing endovascular thrombectomy for ischemic stroke. The primary outcome is the hospital’s door-to-groin time. The study starts with a 6-month period in which none of the hospitals receives the performance feedback intervention. Subsequently, every 6 months, three or four hospitals are randomized to cross over from the control to the intervention conditions, until all hospitals receive the feedback intervention. The feedback intervention consists of a dashboard with quarterly reports on patient characteristics, structure, process, and outcome indicators related to patients with ischemic stroke treated with endovascular thrombectomy. Hospitals can compare their present performance with their own performance in the past and with other hospitals. The performance feedback is provided to local quality improvement teams in each hospital, who define their own targets on specific indicators and develop performance improvement plans. The impact of the performance feedback and improvement plans will be evaluated by comparing the primary outcome before and after the intervention.

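### The unadjusted Kruskal-Wallis and chi-square comparisons ignore calendar time and hospital, are not ranked below the mixed model for door-to-groin time, and are the only effect analysis stated for the secondary outcomes

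*Protocol article*

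**What the plan says.** Two analyses of the same effect stand side by side in the Statistical methods section.

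- The opening paragraph assesses the effect on the primary and the secondary outcomes by "comparing median/percentage outcomes between control and intervention cluster periods", "using a non-parametric Kruskal-Wallis test and Pearson’s chi-square statistic, respectively". This covers all outcomes. The tests have no term for hospital or for time.
- The next paragraph, for door-to-groin time only: "Generalized linear mixed modeling at the individual patient level will be used for analyzing the effect" of the intervention. That model contains "calendar time (month) to account for autonomous time trends", patient characteristics "and a random effect for the hospital".

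Neither analysis is called primary, confirmatory or descriptive. The sensitivity analyses that follow also concern the primary outcome only. For door-to-needle time, eTICI, NIHSS at 24 h and mRS at 3 months, the opening paragraph is therefore the only stated analysis of the intervention effect.

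The abstract says that the impact "will be evaluated by comparing the primary outcome before and after the intervention", with no mention of adjustment for time.

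**The concern.** In a stepped wedge, the share of hospitals under intervention rises with calendar time by design. A raw comparison of the two conditions therefore mixes the effect of feedback with whatever else changed over 30 months. Background shortening of door-to-groin time would be credited to feedback, and background lengthening could hide a real benefit. The plan evidently expects such trends, because it gives them as the reason for the month term in the mixed model.

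The second weakness is clustering. The Power calculation section uses an ICC of 0.37. A rank test on pooled patients ignores it and overstates the information in the data.

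For the primary outcome, two p-values of very different validity could each be reported as the trial's answer. For the secondary outcomes, the only stated p-value is the unprotected one.

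**Working it through.** **1. Inputs.** From Trial design and Power calculation: 13 hospitals; four steps of 3, 3, 3 and 4; five 6-month periods; mean 77 min, SD 47 min; ICC 0.37; 30 patients per hospital per 3 months; target 10 min; alpha 5% (taken as two-sided, which is not stated). Assumed: the size of any secular trend, shown as a range because the protocol gives none.

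Variances: total 47² = 2209; between hospitals 0.37 × 2209 = 817.3 (SD 28.6); within hospitals 0.63 × 2209 = 1391.7 (SD 37.3).

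**2. The plan's own power figure.** The Hussey-Hughes variance is

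Var = Iσ²(σ² + Tτ²) / [(IU − W)σ² + (U² + ITU − TW − IV)τ²].

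Take three hospitals per step (I = 12), T = 5 and 30 patients per hospital-period. Then σ² = 1391.7/30 = 46.39, τ² = 817.3, U = 30, W = 270 and V = 90.

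- Numerator: 12 × 46.39 × (46.39 + 4086.7) ≈ 2,300,700.
- Denominator: 90 × 46.39 + 270 × 817.3 ≈ 224,850.
- Var ≈ 10.23, SE ≈ 3.20, power = Φ(10/3.20 − 1.96) ≈ 87.8%.

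This matches the stated 88%. With all 13 hospitals it is 89.8–90.3%. With 60 patients per 6-month step it is 99.5–99.6%; that difference is a separate matter. The stated power thus belongs to a time- and cluster-adjusted analysis, not to the rank test.

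**3. Distance in calendar time.** Number the periods 0 to 4 and put the group of four last.

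- Control hospital-periods: 3×1 + 3×2 + 3×3 + 4×4 = 34. Sum of indices 0 + 3 + 9 + 24 = 36; mean 36/34 = 1.06.
- Intervention hospital-periods: 3×4 + 3×3 + 3×2 + 4×1 = 31. Sum of indices 30 + 27 + 21 + 16 = 94; mean 94/31 = 3.03.
- Gap: 1.97 periods × 6 = 11.8 months. With the group of four first, 100/34 − 30/31 gives the same 1.97.

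Bias of the raw contrast = yearly trend × 11.84/12. An assumed fall of 5 min per year gives 4.9 min; 10 min per year gives 9.9 min.

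**4. False-positive rates.** Simulation with no true effect: normal outcomes, linear trend, 2000 trials per row. The adjusted analysis is a random-intercept GLS with fixed period effects and known variances, standing in for the mixed model. Each cell gives the result for 30 / 60 patients per hospital-period.

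| Assumed trend, min per year | Kruskal-Wallis, pooled patients | Kruskal-Wallis, hospital-period medians | Time- and hospital-adjusted |
|---|---|---|---|
| 0 | 57.6% / 68.6% | 5.7% / 6.0% | 6.0% / 4.6% |
| −4 | 62.2% / 72.5% | 10.8% / 11.2% | 4.5% / 4.2% |
| −8 | 74.1% / 81.9% | 23.6% / 25.8% | 3.8% / 5.0% |
| −10 | 80.8% / 85.4% | 31.0% / 35.9% | 5.1% / 5.2% |

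Repeat runs with no trend gave up to about 70% on pooled patients and up to about 8% on medians, hence the upper ends of the ranges quoted.

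**5. The opposite direction.** With a true 10 min reduction and an assumed rise of 10 min per year, the raw difference in medians averages only −0.4 min. The test on hospital-period medians then rejects in about 5% of trials. The adjusted analysis keeps 90% power (30 per period) to 99% (60 per period).

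**The case against.** The strongest reply is that the right analysis of the primary outcome is already in the plan. The mixed model adjusts for month and hospital, is the only analysis described in detail, and rests on the same methodological source as the power calculation. The opening paragraph can be read as the customary unadjusted summary before it, and a condensed article may leave the ranking to an analysis plan. This stands in part: a reader might infer that the trial has no valid analysis of door-to-groin time, and the document does not support that. What remains is that the article names significance tests and says that they assess the effect, which goes beyond a summary, and gives no order of precedence. The reply also does nothing for the secondary outcomes. The case-mix adjustment mentioned under the dashboard indicators uses baseline characteristics, not calendar time.

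Three further readings would go too far.

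- That the rank test rejects a true null most of the time. This holds only if patients are pooled. The wording about cluster periods, and the aggregation into hospital-level medians under Data collection and management, allow a hospital-period unit, for which the rate without a trend is near nominal.
- That control and intervention are fully separated in time. Only the first period is all control and only the last all intervention; the three between contain both, so confounding is partial.
- That the abstract commits the trial to an unadjusted before-after contrast. Its sentence names no test and can be squared with an adjusted model; it is loose rather than contradictory.

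**Conclusion.** The point holds in this form. The article states a test of the intervention effect that allows for neither calendar time nor hospital, in a design where intervention data lie on average 11.8 months later than control data. The gap follows from the design alone. The bias is conditional on a trend: about 4.9 min at an assumed 5 min per year and about 9.9 min at 10 min per year. The error rate depends on a unit that the article does not fix: about 58–70% on pooled patients even with no trend; on hospital-period medians, about 6–8% with no trend and about 31–36% at 10 min per year. Both versions fail under the kind of trend that the plan itself anticipates. For door-to-groin time the defect is one of ranking, since a suitable model is also stated. For the secondary outcomes it is more serious, because no adjusted analysis is stated. The simulated rates further assume normal outcomes, equal numbers per hospital and a linear trend.

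**What to change.** - Name the mixed model with calendar time and a random hospital effect as the sole test of the effect on door-to-groin time.
- For each secondary outcome, specify an analogous mixed model suited to its type, with fixed calendar time and a random hospital effect. This must accompany the next change; otherwise removing the raw p-values leaves these outcomes with no stated test.
- Keep medians and percentages by condition and period as descriptive summaries without p-values.
- Reword the abstract's sentence so that it refers to the time-adjusted comparison.

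The cost is wording, a little more analysis work, and less precise estimates for the secondary outcomes than the raw comparison would appear to give. No new data are needed.

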## Methods

### Trial design

We designed a stepped wedge cluster randomized trial (CRT) of performance feedback on the quality of care in hospitals performing EVT for ischemic stroke (PERFEQTOS) to determine the impact of a performance feedback intervention accompanying hospital-specific action plans and improvement targets. This is a specific form of CRT in which initially all clusters (in this study: hospitals) serve as controls. The intervention is rolled out sequentially but randomly at different time points, such that at the end of the study all clusters have crossed over to the intervention condition (Fig. 1) [22]. In the present study, the design includes an initial 6-month period in which none of the hospitals receives performance feedback. Subsequently, every 6 months, three or four randomly chosen hospitals will cross over from control to intervention conditions, which implies a total study duration of 30 months given that 13 hospitals participate. The Standard Protocol Items: Recommendation for Interventional Trials (SPIRIT) checklist [23] is shown in Additional file 1.

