### Power calculation

The power calculation was based on mean differences in door-to-groin time as a primary outcome. We used a parametric power estimation methodology for stepped wedge designs put forward by Hemming and Girling [39] in the Stata function stepped wedge, derived from Hussy and Hughes [40]. We assumed 13 EVT centers were randomized in four clusters per time step (three clusters of three hospitals and one cluster of four hospitals) that treated an average of 30 patients per center per time period of 3 months [21]. We used a mean door-to-groin time of 77 min (standard deviation 47 min) and *ICC* 0.37, both obtained from the MR CLEAN Registry data [21, 24]. Assuming a significance level of 5%, this would result in 88% power to detect a clinically relevant reduction of door-to-groin time of 10 min.

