## Discussion

PERFEQTOS is a stepped wedge cluster randomized trial about the effect of performance feedback on the quality of acute ischemic stroke care. This performance feedback consists of a multifaceted intervention, including the implementation of a quality indicator dashboard, quality improvement teams, and performance improvement plans. The primary outcome is a process measure (door-to-groin time) which is actionable and strongly associated with clinical outcomes [6].

Previously, it has been noticed that a stepped wedge CRT design is more efficient when the intra-cluster correlation (*ICC*) is moderate or high (*ICC* ≥ 0.1) [42, 43]. Generally, *ICC* tends to be higher for process indicators in comparison to clinical outcomes, which is related to the fact that processes can be more easily influenced by providers than outcomes [43]. Therefore, since our main focus is on improving care processes through performance feedback, a stepped wedge CRT design is an efficient design for this study. Another strength of the stepped wedge CRT design is that it provides an opportunity to measure the effect of duration of exposure to the intervention as well as of underlying temporal changes. In order to take advantage of this strength, the longitudinal time intervals should be sufficiently broad [40]. We hypothesize 6 months is long enough to achieve an effect based on treatment outcome measurements (e.g., functional outcome at 3 months after stroke). This design helps us also to tackle difficulties of implementation of the intervention at all hospitals at once. Additionally, the intervention effect in all hospitals can be evaluated with different time exposures (6–18 months).

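### The Kruskal-Wallis/chi-square test of time trends among intervention periods compares changing sets of hospitals, so with no trend at all it rejects in about 60-80% of trials at the protocol's ICC

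*Protocol article*

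**What the plan says.** Statistical methods opens with an unadjusted analysis of all outcomes, primary and secondary, presented as an assessment of the intervention effect. Its first part sets control periods against intervention periods. Its second part, the subject of this point, looks for differences "also in the time trends of intervention cluster periods using a non-parametric Kruskal-Wallis test and Pearson’s chi-square statistic, respectively". No hospital term, stratification or fixed set of hospitals is attached to it.

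The roll-out is in Trial design: after a 6-month control period, "every 6 months, three or four randomly chosen hospitals will cross over from control to intervention conditions". Power calculation gives the grouping as "three clusters of three hospitals and one cluster of four hospitals".

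Statistical methods also describes a patient-level mixed model with a hospital random effect and calendar month, and sensitivity analyses on duration of exposure. Both are specified for door-to-groin time only. The Discussion counts it as a strength of the design that "it provides an opportunity to measure the effect of duration of exposure to the intervention as well as of underlying temporal changes".

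**The concern.** The question is whether outcomes change over time once hospitals receive feedback. The Kruskal-Wallis and chi-square null is different: that all patients in the compared periods are exchangeable, whichever hospital treated them. The stepped wedge makes that null false without any change over time, because the hospitals contributing to each period differ.

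- By calendar period, the intervention group holds 3, 6, 9 and 13 hospitals if the group of four crosses last, or 4, 7, 10 and 13 if it crosses first.
- By time since crossover, all 13 hospitals contribute to the first 6 months and only the first wave to the last.

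A significant result would be read as feedback gaining strength or wearing off, when it mostly reflects which hospitals the lottery drew first. The direction is arbitrary: if slow hospitals are drawn first, later calendar periods look faster, and the reverse if fast ones are. For door-to-groin time the result could contradict the planned exposure-duration analysis. For door-to-needle time, eTICI, NIHSS and mRS there is no other stated trend analysis to set against it.

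**Working it through.** **Inputs (Power calculation, Trial design).** 13 hospitals in waves of 3, 3, 3 and 4; five 6-month periods; mean 77 min, SD 47 min; ICC 0.37; 5% level, taken as two-sided. The text says each center "treated an average of 30 patients per center per time period of 3 months", so 60 per 6-month period.

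**The plan's own figure.** The article states no error rate for the trend test; its only computed figure is 88% power for a 10-min reduction. The Hussey-Hughes variance is

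Nσ²(σ² + Tτ²) / [(NU − W)σ² + (U² + NTU − TW − NV)τ²],

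with τ² = 47² × 0.37 = 817.3 and, at 30 patients per period, σ² = 47² × 0.63 / 30 = 46.4. With three hospitals per step, N = 12, T = 5, U = 30, W = 270 and V = 90. The standard error is 3.20 min, 10/3.20 − 1.96 = 1.17, and power is 87.8%. The 88% is therefore reproduced with SD 47 as the total SD and 30 patients per hospital per step. With all 13 hospitals the same formula gives 90.3%, and with 60 patients per step 99.6%. Because 88% corresponds to 30 per step and the text implies 60, both are carried below.

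**Size of the artefact by hand.** The between-hospital SD is √817.3 = 28.6 min. Compare the first intervention period (3 hospitals) with the last (all 13, including those 3), with nothing changing over time. The SD of the difference due to hospital mix alone is

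√[817.3 × (1/3 − 1/13)] = √209.6 = 14.5 min.

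Treating the 3 × 60 = 180 and 13 × 60 = 780 patients as independent, the sampling error is

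47 × √(1/180 + 1/780) = 3.9 min.

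The mix artefact is typically more than three times the error that such a test allows for, and larger than the 10-min effect the trial targets.

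**Simulated false-positive rate.** Outcome = 77 + hospital effect N(0, 47² × ICC) + residual N(0, 47² × (1 − ICC)); no intervention effect and no trend; Kruskal-Wallis on patients under intervention, grouped by period; nominal 5%.

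| ICC | 60 per hospital-period: calendar / exposure | 30 per hospital-period: calendar / exposure |
|---|---|---|
| 0.37 (stated) | 79% / 79% | 60% / 61% |
| 0.10 (assumed) | 43% / 44% | 26% / 24% |
| 0.05 (assumed) | 26% / 26% | 17% / 15% |
| 0.02 (assumed) | 14% / 13% | 9% / 9% |
| 0.01 (assumed) | 9% / 9% | 7% / 6% |
| 0 | 5% / 5% | 5% / 5% |

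Pearson chi-square by calendar period at ICC 0.37, with 60 and 30 patients, gives about 80-81% and 62-64% (beta-binomial, event rates 0.4 and 0.6) or 71% and 50% (dichotomised normal).

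**Robustness at ICC 0.37, 60 patients.** Lognormal outcome 79%; group of four crossing first 75%; quarterly instead of 6-monthly intervention periods 69%.

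**Isolating the cause, same null and ICC.** Kruskal-Wallis on ranks taken within each hospital rejects in 3.5%. With one fixed set of hospitals followed over four periods it rejects in 0.8% (all 13) or 2.3% (first three). The excess disappears once the hospital mix is held constant or removed.

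**The case against.** The arithmetic under pooling is not in dispute; the reading and the weight can be.

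1. **The grouping is not spelled out.** Data collection and management mentions hospital-level medians and percentages. Kruskal-Wallis on hospital-period medians would almost never reject (about 0.05%), and a trend within a single hospital rejects in under 4%. This stands as a condition on the headline figure. Pooling patients is still the natural reading: outcomes are collected per patient, Pearson's chi-square needs counts, and the aggregation is described as feeding the dashboard. A 5% test that rejects in about 0.05% of trials would not be valid either.
2. **The ICC of 0.37 belongs to door-to-groin time,** where a mixed model and an exposure-duration analysis are already planned. This stands. The Discussion expects lower ICCs for clinical outcomes, so 79% must not be carried over to NIHSS or mRS. Door-to-needle time, however, is a process measure, and even an ICC of 0.02 more than doubles the error rate at 60 patients.
3. **The 60% end uses half the stated number of patients.** Correct: on the stated 30 per 3 months the figure is about 79%. The lower value is kept because the stated power corresponds to 30 per step.
4. **The control-versus-intervention test in the same sentence has a related fault** (about 70% false positives at ICC 0.37 and 60 patients). True, but it answers a different question and does not excuse the trend test.
5. **A fuller analysis plan may hold models for the secondary outcomes.** Possibly. The point does not rest on a missing model: the article names a specific test as an assessment of the intervention effect, and that test is invalid.

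**Conclusion.** The trend test is wrong as written. With patients pooled by intervention period, it confounds hospital mix with time and, at ICC 0.37, rejects a true null in about 79% of trials with 60 patients per hospital-period and about 60% with 30, whether periods are ordered by calendar or by exposure. For the secondary outcomes the size depends on ICCs the article does not give; assumed values of 0.02 to 0.10 give about 14% to 43% for Kruskal-Wallis with 60 patients. These figures assume a normal hospital random intercept and equal numbers of patients per hospital; a skewed outcome or the other wave order changes them little. The primary mixed model is not affected, and no decision rule is tied to the trend p-value. This should be corrected, but it does not threaten the main inference.

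**What to change.** Delete the Kruskal-Wallis and chi-square test of time trends among intervention cluster periods. Show medians and percentages by intervention period as description without p-values, or for a fixed set of hospitals such as one wave.

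Assess the trend under intervention within hospitals: add time since crossover (6-month categories or a linear term) to the mixed model that already contains hospital, calendar time and intervention. Do this for door-to-groin time and for each secondary outcome, with a linear, ordinal or logistic form as the scale requires. In a simulation with no exposure trend and a common secular change of −2 min per period, a hospital-period-level model with these terms rejected for the exposure-time term in 4.1% of trials.

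The cost is analysis wording, one extra model per secondary outcome, and an exposure-time estimate less precise than the pooled comparison appears to be. No new data are needed.

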Outcome indicators are post-EVT reperfusion grade of the Extended Thrombolysis in Cerebral Infarction (eTICI) score, ranging from 0 (no reperfusion) to 3 (full reperfusion), and the National Institute of Health Stroke Scale (NIHSS) score at 24 h (± 12 h), which quantifies the neurological deficit caused by a stroke (range 0–42). In addition, the modified Rankin Scale (mRS) score is used as a measure of patients’ functional outcome after acute ischemic stroke, ranging from 0 (no symptoms) to 6 (death). The mRS score is assessed 3 months after admission. Since the outcome is strongly associated with baseline patient characteristics [35], patients’ age, sex, NIHSS score on arrival, location of the proximal intracranial occlusion, and time from onset to arrival at the intervention hospital (onset-to-door time) are also collected. Stroke onset is defined as the time point when stroke symptoms were first noticed by the patient or an observer. In cases the time of first symptoms is unknown, onset is defined as the moment the patient was last seen well. Additionally, we adjusted the outcomes per hospital for differences in these baseline characteristics.

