### Study outcomes

The primary outcome is door-to-groin time. Secondary outcomes are door-to-needle time, eTICI score, NIHSS at 24 h, and mRS at 3 months (Table 1). These outcomes are collected for every individual patient (Table 1).

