The (design of the) current study has some limitations. First, given that our intervention is multifaceted, it may be difficult to disentangle the relative impact of the different aspects of the intervention. However, an intervention with a combination of different strategies is more effective than approaches using a single intervention [44]. Second, the quality improvement policies of hospitals in the control phase are heterogeneous and this may influence the effect of our intervention. To facilitate the interpretation of our results, we will use semi-annual questionnaires to obtain insight into the quality improvement policies of the hospitals in the control arm. Third, outcome assessment is not blinded in our trial. However, the primary outcome (door-to-groin time) is an objective measure and therefore unlikely to bias the trial results. The assessment of the secondary outcomes NIHSS at 24 h and mRS at 3 months is not blinded as well, but because these outcomes are routinely collected through a structured algorithm, we expect the risk of bias to be limited.

Findings from this study will provide insight into the feasibility and effectiveness of structured performance feedback in reducing the time to treatment of patients with ischemic stroke treated with endovascular thrombectomy and, thereby, in improving patient outcomes. If the expected results are realized, the developed method for performance feedback is ready for wider implementation on a national and international level and can be adapted for use in other diseases.

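### The four secondary outcomes get only unadjusted control-versus-intervention tests, so any shared time trend in this stepped wedge enters their estimated feedback effect

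*Protocol article*

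**What the plan says.** The Statistical methods section sets out two analyses.

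- For all outcomes: "The effect of the intervention on the primary and secondary outcomes will be assessed by comparing median/percentage outcomes between control and intervention cluster periods", "using a non-parametric Kruskal-Wallis test and Pearson’s chi-square statistic, respectively". The same sentence applies these tests to time trends within the intervention periods.
- A patient-level generalized linear mixed model with fixed effects for intervention, "calendar time (month) to account for autonomous time trends" and five baseline characteristics, "and a random effect for the hospital". This model "will be used for analyzing the effect of the performance feedback intervention on the primary outcome (door-to-groin time"). The variance estimates and the sensitivity analyses on exposure duration are also tied to the primary outcome.

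Under Study outcomes: "Secondary outcomes are door-to-needle time, eTICI score, NIHSS at 24 h, and mRS at 3 months". No section extends the model to these four.

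The section on indicator measurement for the dashboard says: "Since the outcome is strongly associated with baseline patient characteristics". It then reports adjusting outcomes per hospital for baseline differences. The Discussion expects insight into "reducing the time to treatment of patients with ischemic stroke treated with endovascular thrombectomy and, thereby, in improving patient outcomes".

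**The concern.** In a stepped wedge, exposure to the intervention rises with calendar time by construction. A contrast without a time term cannot separate feedback from whatever else changed nationally over 30 months. The article accepts this for door-to-groin time, since it justifies the model by time trends and by the hierarchy of patients within hospitals. Both reasons apply equally to the secondary outcomes of the same patients in the same hospitals.

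The article names the secondary-outcome method, so this is not a detail left open for an analysis plan. If the text is followed, a general improvement in reperfusion, thrombolysis times or functional outcome would be counted as an effect of feedback. Three of the four outcomes (eTICI, NIHSS, mRS) are the trial's only direct evidence on patient outcomes.

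**Working it through.** **The plan's own figure.** The article gives no error rate, power or ICC for a secondary outcome. Its only such figure is 88% power for a 10-minute reduction in door-to-groin time. The Hussey-Hughes formula (5 periods, SD 47, ICC 0.37) with 12 hospitals and 30 patients per period gives a standard error of 3.199 min, and Φ(10/3.199 − 1.96) = 87.8%. With 13 hospitals it gives 89.8-90.3%, and with 60 patients per 6-month step 99.5-99.6%. That difference does not bear on this point. What matters is that the formula presupposes period and hospital effects, which the secondary analyses lack.

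**Inputs from the article.** 13 hospitals; four crossover groups (three of 3, one of 4); five 6-month periods; 30 patients per centre per 3 months, hence 60 per period; 5% level, taken as two-sided. **Assumed:** a 40% binary outcome, ICC 0 to 0.10, a linear trend, no intervention effect, and the group of four crossing last.

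**Step 1: timing gap.** Number the periods 0 to 4.
- Intervention hospital-periods: 3×4 + 3×3 + 3×2 + 4×1 = 31. Control: 65 − 31 = 34.
- Mean intervention period: (3×10 + 3×9 + 3×7 + 4×4)/31 = 94/31 = 3.03.
- Mean control period: (130 − 94)/34 = 1.06.
- Gap: 1.97 periods, or about 12 months. If the group of four crosses second or third, the gap is 2.03.

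Spurious difference = 1.97 × drift per period. A 5-point change from first to last period is 1.25 points per period, giving 1.97 × 1.25 = 2.47 points.

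**Step 2: patient-level test.** Let v = 0.4 × 0.6 = 0.24 and f = 1/1860 + 1/2040 = 0.001028. The test uses SE = √(v·f) = 1.57 points and rejects beyond 1.96 × 1.57 = 3.08 points. The true variance is ICC·v·S + (1 − ICC)·v·f, where S = Σ(xᵢ/31 − (5 − xᵢ)/34)² and xᵢ is the number of intervention periods of hospital i:

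S = 3×0.0996² + 3×0.0380² + 3×0.0237² + 4×0.0854² = 0.0649.

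| ICC | True SD (points) | Rejects, no trend | Rejects, 5-point trend |
|---|---|---|---|
| 0 | 1.57 | 5% | 35% |
| 0.01 | 2.00 | 12% | 38% |
| 0.05 | 3.18 | 33% | 46% |
| 0.10 | 4.22 | 47% | 54% |

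Independent simulations agree. With no trend they give 13-15%, 33-34% and 45-48% at ICC 0.01, 0.05 and 0.10. With a 5-point trend they give 35-55% across ICC 0 to 0.10.

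**Step 3: tests on hospital-period summaries.** Kruskal-Wallis on the 65 hospital-period percentages, simulated:
- No trend: about 5-6%.
- 5-point trend: about 31%, 23%, 13% and 12% at ICC 0, 0.01, 0.05 and 0.10. The overall range is about 12-32%, and single runs at ICC 0.10 gave 10-13%.

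On a time scale, borrowing the SD of 47 min and assuming a drift of −2.5 min per period, Kruskal-Wallis on hospital-period medians rejects 70% (ICC 0) and 35% (ICC 0.05). On patients it rejects 89% and 75%.

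**Step 4: with hospital and period effects.** On a continuous outcome with known variance components, the null estimate stays within 0.11 min of zero and rejection is 4.2-5.5% for every drift and ICC tried. A linear probability model for the binary outcome gives 4.4-5.9%.

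**The case against.** **Unit of analysis.** The article speaks of comparing medians and percentages between cluster periods, and under Data collection and management of aggregating to hospital level. If hospital-periods are the unit, the inflation from clustering largely disappears. This stands, and the text is ambiguous: individual-level collection and Pearson's chi-square point to patients. Drift bias survives on either reading.

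**Hospital mix.** A reader might infer that hospital mix biases the result towards feedback. It does not. Crossover order is randomized, so hospital mix is a chance imbalance that inflates error in either direction. Only drift is systematic.

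**What the patient-outcome claim rests on.** A reader might infer that it rests entirely on the four secondary outcomes. The documents do not support that. Door-to-needle time is a process indicator in Table 1, and the Discussion argues partly through the modelled primary outcome.

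**Existing adjustments.** The baseline adjustment in the dashboard section may soften the case-mix point, but it has no time or clustering term. The tests on time trends within intervention periods do not adjust the control-intervention contrast.

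**Validity of the fix.** The checks in Step 4 used linear models, so they do not validate ordinal mixed models. They also assume no hospital-by-period variation. If 20% of the between-hospital variance is period-specific and the model omits it, rejection rises to about 6%, 12% and 20% at ICC 0.01, 0.05 and 0.10. The fix is better than the pooled tests, but it is not shown to hold exactly 5%.

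**Source.** This is a condensed article, and a fuller plan might extend the model. Because the article itself names the method, that defence is weak.

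**Conclusion.** The point holds for calendar time on any reading, and for clustering if patients are the unit of the tests. As written, the secondary contrasts carry about twice any per-period drift. False-positive rates with no trend are about 13%, 33% and 47% at ICC 0.01, 0.05 and 0.10 for patient-level tests, and about 5-6% for hospital-period summaries. With a 5-point trend they are 35-55% and about 12-32% respectively.

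Only the 1.97-period gap follows from the design, and it moves to 2.03 at most with the order of the groups. The event rate, ICCs and trend sizes are assumptions, because the article gives none for secondary outcomes and defines no binary one. Door-to-needle time is measured only in non-transferred patients, so fewer than 60 per period would contribute. The primary mixed-model analysis is unaffected. The correction should be made before the secondary results are interpreted as effects of feedback.

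**What to change.** In Statistical methods, extend the mixed model to the primary and each secondary outcome, with intervention, calendar time, the listed baseline characteristics and a hospital random effect:

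- mRS and eTICI: an ordinal (for example proportional-odds) mixed model.
- Door-to-needle time (non-transferred patients) and NIHSS at 24 h: a linear mixed model on a suitable scale.
- Preferably a small-sample correction for 13 hospitals, with a hospital-by-period random effect considered as a sensitivity analysis.

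Base secondary effects and intervals on these models. Present the pooled medians and percentages descriptively, and state whether they summarise patients or hospital-periods.

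The variables are already collected, so the cost is wording and modest programming. Intervals will be wider: for a 40% binary outcome the standard error is about 2.8 points under hospital and period adjustment, against the 1.57 points that the pooled test assumes.
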